## Abstract

**Background:**

There is an ever-growing number of patients requiring aortic valve replacement (AVR). Limited data is available on the long-term outcomes and structural integrity of bioprosthetic valves in younger patients undergoing surgical AVR.

**Methods:**

The INSPIRIS RESILIA Durability Registry (INDURE) is a prospective, open-label, multicentre, international registry with a follow-up of 5 years to assess clinical outcomes of patients younger than 60 years who undergo surgical AVR using the INSPIRIS RESILIA aortic valve. INDURE will be conducted across 20–22 sites in Europe and Canada and intends to enrol minimum of 400 patients. Patients will be included if they are scheduled to undergo AVR with or without concomitant root replacement and/or coronary bypass surgery.

The primary objectives are to 1) determine VARC-2 defined time-related valve safety at one-year (depicted as freedom from events) and 2) determine freedom from stage 3 structural valve degeneration (SVD) presenting as morphological abnormalities and severe haemodynamic valve degeneration at 5 years. Secondary objectives include the assessment of the haemodynamic performance of the valve, all stages of SVD, potential valve-in-valve procedures, clinical outcomes (in terms of New York Heart Association [NYHA] function class and freedom from valve-related rehospitalisation) and change in patient quality-of-life.

**Discussion:**

INDURE is a prospective, multicentre registry in Europe and Canada, which will provide much needed data on the long-term performance of bioprosthetic valves in general and the INSPIRIS RESILIA valve in particular. The data may help to gather a deeper understanding of the longevity of bioprosthetic valves and may expand the use of bioprosthetic valves in patients under the age of 60 years.

**Trial registration:**

ClinicalTrials.gov identifier: NCT03666741 (registration received September, 12th, 2018).

## Background

There is an ever-growing number of patients requiring aortic valve replacement (AVR) [1]. The two principal reasons for AVR are aortic regurgitation (AR) and aortic stenosis (AS), the latter being the most common indication. Although the majority of patients is older [2], younger patients are of particular concern as they have a longer lifespan with their replaced valve and are dependent on properly functioning, non-deteriorated valves over this much longer term.

In general, a wide spectrum of therapies can be offered to younger patients such as sparing valve techniques and mechanical valve replacement. Homografts are possible but less popular due to inferior longevity. The Ross procedure gains in popularity in selected expert centres. Mechanical valves have been preferred over bioprosthetic valves in younger patients, but this is not equivocal. While some studies have shown a survival benefit of mechanical valves in younger patients [3–7], large retrospective observational studies [8–12] and one randomized controlled trial [13] have shown similar long-term survival in patients 50 to 69 years of age undergoing mechanical versus bioprosthetic valve replacement.

Based on these data, the 2017 American Heart Association (AHA)/American College of Cardiology (ACC) guidelines on valvular heart disease [14] recommend mechanical over bioprosthetic valves in patients below the age of 50 years (class IIa, lowered from 60 years in the 2014 version) and suggest an individualised choice (so called grey-zone) of either a mechanical or bioprosthetic valve in patients between 50 and 70 years. Conversely, the 2017 European guidelines recommend the use of mechanical valves in patients under the age of 60 years unless good quality anticoagulation is unlikely and a grey zone between 60 and 65 years [15]. Both guidelines emphasize the need to consider the desire of an informed patient when it comes to the choice of the valve treatment.

The INSPIRIS RESILIA aortic Valve™ (Edwards Lifesciences, Irvine, USA) is a stented bioprosthetic, tri-leaflet valve comprised of bovine pericardial tissue. Specific new tissue preservation techniques result in a stable capping process, which blocks residual aldehyde groups known to bind calcium, in addition to a phospholipid removal process. A final tissue glycerolisation step allows valve storage without further tissue exposure to glutaraldehyde. Finally, INSPIRIS RESILIA features an expansion feature, called VFit, intended for future potential valve in valve procedures.

RESILIA tissue demonstrated, in a large pre-clinical randomized control trial conducted in juvenile sheep in mitral position, to significantly reduce tissue calcification (− 72%) and even to improve haemodynamic performance compared with the Perimount valve [16]. The RESILIA tissue also has been studied in two clinical trials to date [17, 18]. Bartus et al. found, in a single-arm observational study of 133 patients, that the RESILIA tissue provided excellent performance and safety without structural valve deterioration (SVD) [18–20]. In the COMMENCE trial [17, 20], 679 patients underwent Carpentier-Edwards PERIMOUNT Magna Ease™ aortic valve replacement with RESILIA™ tissue (Model 11000A) and similar excellent safety and effectiveness were demonstrated for up to 4 years without SVD. Both of these trials have included relatively young patients, with a mean age between 65 and 67 years and up to 26% of patients aged less than 60 years.

These trials generated useful insights on the safety and effectiveness of the RESILIA tissue, but they were not specifically designed to assess durability in younger patients which received the INSPIRIS RESILIA aortic valve and data on this topic in general is scarce [21, 22].

It is for this reason that we designed a prospective long-term registry around the INSPIRIS RESILIA aortic Valve™. With 400 patients under the age of 60 years included and a follow-up of 5 years, we will collect data on the short-term clinical effectiveness of the valve’s implantation, as well as pivotal data on the long-term haemodynamic and structural performance of the valve.

## Methods/design

The INDURE registry is a prospective, open-label, multicentre, international registry with a follow-up of 5 years to assess the clinical outcomes of patients younger than 60 years of age who undergo surgical AVR with the INSPIRIS RESILIA aortic valve (Edwards Lifesciences). The registry is conducted according to ISO 14155:2011. Approximately 400 patients will be enrolled across 20–22 European sites (including Austria, Belgium, France, Germany, Italy, the Netherlands, Spain, and UK) and Canada, resulting in about 20 patients per site. It was estimated, from the COMMENCE Trial dataset [17, 20], that freedom from time-related valve safety events at 1-year (composite endpoint according to VARC-2 criteria) is around 91.5%, suggesting that 400 patients will arrive at a 95% confidence interval (CI) of ±2.14%. Lower rates (80%) will broaden the 95% CI to ±3.92% and higher rates (99%) narrow it down to ±1%.

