### Objectives

The primary objectives (Table 1) are to 1) determine the time-related valve safety at 1-year (composite endpoint according to the VARC-2 criteria) depicted as freedom from events [23] and 2) determine freedom from stage 3 SVD following the Salaun definition at 5 years [23, 24]. Events include SVD (either valve-related dysfunction, defined by haemodynamic parameters or the need for repeat procedure), prosthetic valve endocarditis, prosthetic valve thrombosis, thromboembolic events (e.g., stroke) and valve-related bleeding.

**Table 1 Tab1:** Registry objectives

**Primary objectives**	Time-related valve safety at 1 year (composite endpoint according to VARC-2 [23] depicted as freedom from the following events: • SVD (valve-related dysfunction [MPG ≥20 mmHg, EOA ≤0.9–1.1 cm^2^ and/or DVI < 0.35 m/s, AND/OR moderate or severe prosthetic valve regurgitation], requiring repeat procedure [TAVI or SAVR]) • Valve-related dysfunction • Requirement of repeat procedures (Re-intervention) • Prosthetic valve endocarditis • Prosthetic valve thrombosis • Thromboembolic events (e.g., stroke) • Valve-related VARC bleeding
	To determine freedom from stage 3 SVD following [24] at 5 years
**Secondary objectives**	Haemodynamics and durability: • Haemodynamic performance of the INSPIRIS RESILIA Aortic Valve™ including PPM • SVD following Salaun [24] • Description of potential ViV procedures and clinical outcome including follow-up
	Clinical outcomes: • NYHA functional class compared to baseline • Freedom from valve-related rehospitalisation
	Quality-of-life: • 3–6-month, 1-year and 3-year change from baseline in quality-of-life assessed by the KCCQ and SF-12 Health Survey
**Exploratory: Rehospitalisation and costs**	Length of hospital stay
	Length of time in intensive care unit
	Time to return to work
	Rate of valve-related rehospitalisation and associated costs (average costs per country)
	Rate of transfusion for bleeding and associated costs (average costs per country)
	Costs of a major bleeding event
	Costs of daily anticoagulation
	Rate of re-intervention for valve degeneration and associated costs (average costs per country)
**Exploratory: Safety**	SVD
	Non-SVD
	Thromboembolic events (e.g., stroke)
	Valve thrombosis
	All bleeding/haemorrhage
	Major bleeding/haemorrhage
	All paravalvular leak
	Major paravalvular leak
	Endocarditis
	All-cause mortality
	Cardiac-related mortality
	Valve-related mortality
	Valve-related re-intervention
	Conduction disturbances

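### The precision claimed for 400 patients is wrong: at 91.5% freedom from events the 95% CI is ±2.73 points, and the printed ±2.14 belongs to a rate of 95%

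*Protocol article*

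**What the plan says.** The sample size statement is in the Methods/design section of the protocol article. It begins with "Approximately 400 patients will be enrolled". It then takes a planning value for the first primary objective from the COMMENCE dataset: 1-year freedom from time-related valve safety events "is around 91.5%, suggesting that 400 patients will arrive at a 95% confidence interval (CI) of ±2.14" percent. Two sensitivity cases follow: "Lower rates (80%) will broaden the 95% CI to ±3.92% and higher rates (99%) narrow it down to ±1" percent.

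The Objectives section confirms the endpoint, which is to "determine the time-related valve safety at 1-year (composite endpoint according to the VARC-2 criteria) depicted as freedom from events". The article gives no other precision, power or sample size calculation.

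**The concern.** The three half-widths should come from one formula applied to three rates at the same n. The two side cases do. The main case, which is the one the registry was planned on, does not: its half-width is too small for its rate.

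This matters because INDURE has no control group, and the article states no hypothesis or performance goal for this endpoint. Expected precision is therefore the only design property offered in support of 400 patients, and it is wrong in the favourable direction. Taken at face value, the statement implies an interval of 91.5 ± 2.14, or about 89.4% to 93.6%. The design supports a lower limit between about half a point and one point below that, depending on the interval method.

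**Working it through.** **Inputs, all from Methods/design**

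- n = 400
- planning rate p = 0.915
- confidence level 95%, two-sided, so z = 1.96
- printed half-widths: 2.14 at 91.5%, 3.92 at 80%, 1 at 99%

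**Step 1. Identify the formula from the side cases.** The usual normal-approximation half-width is h = z × √(p(1 − p)/n).

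- p = 0.80: 1.96 × √(0.80 × 0.20 / 400) = 1.96 × 0.02000 = 3.92 points. This matches the printed 3.92.
- p = 0.99: 1.96 × √(0.99 × 0.01 / 400) = 1.96 × 0.004975 = 0.975 points. This matches the printed 1 after rounding.

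The formula and n = 400 are therefore those the authors used.

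**Step 2. Apply it to the planning case.**

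- p = 0.915: 1.96 × √(0.915 × 0.085 / 400) = 1.96 × 0.013944 = 2.73 points. The article prints 2.14.
- Interval: 91.5 ± 2.73, or 88.8% to 94.2%.

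**Step 3. Find the rate to which 2.14 belongs.**

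- p = 0.95: 1.96 × √(0.95 × 0.05 / 400) = 1.96 × 0.010897 = 2.136 points, which rounds to 2.14.
- Solving h = 0.0214 for p at n = 400 gives p = 0.950. Allowing for rounding of 2.14, the range is 0.9495 to 0.9500.

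**Step 4. Ask whether another reading gives 2.14 at 91.5%.** Half-widths at n = 400, with 34 events expected (0.085 × 400):

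| Method | Half-width (points) |
|---|---|
| Normal approximation | 2.73 |
| Arcsine | 2.73 |
| Jeffreys | 2.74 |
| Wilson | 2.75 |
| Log-log | 2.77 |
| Agresti-Coull | 2.78 |
| Clopper-Pearson (88.3% to 94.0%) | 2.86 |
| Normal with continuity correction | 2.86 |
| One-sided 95% z value | 2.29 |

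None gives 2.14. Other sample sizes suggested by the article do not help either. Twenty-two sites at 20 patients each make 440, and 1.96 × √(0.915 × 0.085 / 440) = 2.61. The 679 patients of COMMENCE give 2.10.

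**Step 5. Size of the discrepancy.**

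- Ratio: 2.733 / 2.14 = 1.28, so the true interval is about 28% wider.
- n needed for ±2.14 at 91.5%: 1.96² × 0.915 × 0.085 / 0.0214² = 652.4, so 653 patients.
- Confidence level that ±2.14 would have at 91.5% and n = 400: z = 0.0214 / 0.013944 = 1.535, which is about 87.5%.

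**The case against.** The strongest reply concerns consequence. This is a single-arm descriptive registry. No test, power or target precision depends on 2.14, and the article says what interval 400 patients would give, not that 400 was chosen to reach it. The reported interval will come from the observed data, so no estimate is biased. The gap is 0.59 points, and the correct value lies inside the range of 1 to 3.92 that the article itself shows. All of this is true, and it limits the harm to overstated precision. It does not make the planning figure right. That figure is the only stated support for the sample size, so a reader will rely on it.

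A second reply is that the arithmetic shows only a mismatch: the half-width could be as intended and the rate misprinted. This stands in part, because how 2.14 arose cannot be known from the article. But 91.5% is attributed to a named dataset, whereas a 95% rate appears nowhere. Correcting the half-width is the natural reading, subject to the sponsor's confirmation.

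The figure of 653 patients is only a way of expressing the size of the error, since nothing in the article sets ±2.14 as a requirement. Whether the full protocol or the analysis plan repeats the number cannot be seen.

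**Conclusion.** The concern holds. At 91.5% freedom from events and 400 patients, the 95% half-width is 2.73 points, not 2.14. The printed value is about 22% too small (2.14 / 2.733 = 0.78) and matches a 95% rate. The conclusion rests on the article's own n, rate and confidence level, and on the formula that reproduces its other two figures. No standard two-sided 95% interval changes it. The effect is an overstatement of precision for the first primary objective. The validity of the planned analysis is not in question.

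The 2.73 assumes that all 400 patients have a known 1-year status. The article gives no attrition figure. If 10% were not evaluable (an assumption, for illustration only), n = 360 would give 1.96 × √(0.915 × 0.085 / 360) = 2.88 points.

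**What to change.** Confirm that 91.5% is the intended planning rate. If so, replace ±2.14% by ±2.73% in the Methods/design sample size statement, or give the exact interval of 88.3% to 94.0% for 34 events in 400 patients. If 95% was intended, correct the rate and its source, and keep ±2.14%. The side cases at 80% and 99% need no change. Make the same correction in the full protocol and the analysis plan if they carry the figure.

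It would also help, though it is optional, to add the half-width for the number expected to be evaluable at 1 year, for example about ±2.9% for 360.

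If 91.5% stands, the cost is one corrected number and a slightly less favourable precision statement. No patients are added and n = 400 can stand.

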### Patients

Patients under the age of 60 years undergoing SAVR and receiving the INSPIRIS RESILIA aortic valve prosthesis will be enrolled on a consecutive basis. In addition to the applicable criteria of the device Instructions for Use (IFU), the registry inclusion criteria stipulate that patients require a planned replacement of their native valve as indicated in a preoperative evaluation, are scheduled to undergo planned AVR with or without concomitant root replacement and/or coronary bypass surgery. The latter is understood as isolated AVR with or without CABG and ascending aortic replacement. Also allowed is pulmonary vein isolation if it is not a full cox-maze procedure. Patients with a Bentall procedure or any surgery on other valves are not allowed in this registry. Patients need to be available to attend yearly follow-up visits at the registry centre for up to 5 years and all patients are required to provide written informed consent.

Patients will be excluded from the study if 1) they have active endocarditis/myocarditis at the time of surgery or have had it within the last 3 months of the scheduled SAVR, 2) have had previous AVR, 3) valve implantation is not possible in accordance with the device IFU, or 4) they have an estimated life expectancy of less than 12 months for any reason. The intraoperative exclusion criterion is that valve implantation is not possible in accordance with the device IFU.

### Objectives

The primary objectives (Table 1) are to 1) determine the time-related valve safety at 1-year (composite endpoint according to the VARC-2 criteria) depicted as freedom from events [23] and 2) determine freedom from stage 3 SVD following the Salaun definition at 5 years [23, 24]. Events include SVD (either valve-related dysfunction, defined by haemodynamic parameters or the need for repeat procedure), prosthetic valve endocarditis, prosthetic valve thrombosis, thromboembolic events (e.g., stroke) and valve-related bleeding.

**Table 1 Tab1:** Registry objectives

**Primary objectives**	Time-related valve safety at 1 year (composite endpoint according to VARC-2 [23] depicted as freedom from the following events: • SVD (valve-related dysfunction [MPG ≥20 mmHg, EOA ≤0.9–1.1 cm^2^ and/or DVI < 0.35 m/s, AND/OR moderate or severe prosthetic valve regurgitation], requiring repeat procedure [TAVI or SAVR]) • Valve-related dysfunction • Requirement of repeat procedures (Re-intervention) • Prosthetic valve endocarditis • Prosthetic valve thrombosis • Thromboembolic events (e.g., stroke) • Valve-related VARC bleeding
	To determine freedom from stage 3 SVD following [24] at 5 years
**Secondary objectives**	Haemodynamics and durability: • Haemodynamic performance of the INSPIRIS RESILIA Aortic Valve™ including PPM • SVD following Salaun [24] • Description of potential ViV procedures and clinical outcome including follow-up
	Clinical outcomes: • NYHA functional class compared to baseline • Freedom from valve-related rehospitalisation
	Quality-of-life: • 3–6-month, 1-year and 3-year change from baseline in quality-of-life assessed by the KCCQ and SF-12 Health Survey
**Exploratory: Rehospitalisation and costs**	Length of hospital stay
	Length of time in intensive care unit
	Time to return to work
	Rate of valve-related rehospitalisation and associated costs (average costs per country)
	Rate of transfusion for bleeding and associated costs (average costs per country)
	Costs of a major bleeding event
	Costs of daily anticoagulation
	Rate of re-intervention for valve degeneration and associated costs (average costs per country)
**Exploratory: Safety**	SVD
	Non-SVD
	Thromboembolic events (e.g., stroke)
	Valve thrombosis
	All bleeding/haemorrhage
	Major bleeding/haemorrhage
	All paravalvular leak
	Major paravalvular leak
	Endocarditis
	All-cause mortality
	Cardiac-related mortality
	Valve-related mortality
	Valve-related re-intervention
	Conduction disturbances
	Myocardial infarction
	Deep sternal wound infection
	Acute kidney injury

*DVI* Doppler velocity index, *EOA* Effective orifice area, *KCCQ* Kansas City Cardiomyopathy Questionnaire, *MPG* Mean pressure gradient, *NYHA* New York Heart Association, *PPM* Patient prosthesis mismatch, *SAVR* Surgical aortic valve replacement, *SF-12* Short Form-12, *SVD* Structural valve degeneration, *TAVI* Transcatheter aortic valve implantation, *VARC* Valve Academic Research Consortium, *ViV* Valve-in-valve

The secondary objectives are designed to assess haemodynamic performance and further durability parameters, clinical outcomes and quality-of-life (QoL). The first group of objectives is further defined as the haemodynamic performance of the INSPIRIS RESILIA aortic valve including patient prosthesis mismatch (PPM); SVD following the Salaun definition; and the description of potential valve-in-valve procedures and clinical outcomes. Clinical outcomes of interest are NYHA functional class compared to baseline and freedom from valve-related hospitalisation. Quality-of-life will be assessed using the Kansas City Cardiomyopathy Questionnaire (KCCQ) and Short Form-12 Health Survey (SF-12) [24]. Various additional exploratory analyses regarding rehospitalisation, costs and safety will also be performed.

### Data collection

The clinical outcome data collected will be based on the site’s standard-of-care for surgical AVR. Data will be collected prospectively, according to the timetable set out in Table 2, and include medical history, physical assessments, electrocardiogram (ECG), laboratory results, computerised tomography (CT) scans (if performed as a standard-of-care), transthoracic/transoesophageal echocardiography and QoL measures. Anti-thrombotic therapy and medications are at the discretion of each investigator. Data will be captured on an electronic case report form (eCRF) by either a study nurse or physician, and data will be checked automatically for plausibility and completeness.

**Table 2 Tab2:** Data collection schedule

	Baseline/screening	Surgery	Discharge	3–6 months^a^	Years 1–5
Signed informed consent	X				
Medical history^b^	X				
Physical examination^c^	X		X		X
ECG (12-lead)	X		X		X
Echocardiogram (TTE)	X		X		X
Core Lab echo					X^e^
MSCT (if available)					X^f^
NYHA class/CCS angina class	X			X	X
QoL questionnaire (SF-12 and KCCQ)	X			X	X^g^
Anti-thromboembolic therapy and medications	X		X	X	X
Procedural information		X			
Aetiology		X			
SAE reporting		X	X	X	X
Discharge data			X		
Rehospitalisation data^d^				X	X
Return to work				X	X

*CCS* Canadian Cardiovascular Society, *ECG* Electrocardiogram, *KCCQ* Kansas City Cardiomyopathy Questionnaire, *MSCT* Multi-slice computed tomography, *NYHA* New York Heart Association, *QoL* Quality of life, *SAE* Serious adverse event(s), *SF-12* Short Form-12 Health Survey, *TTE* Transthoracic echocardiogram

^a^Data captured over a telephone call

^b^Includes cardiovascular and non-cardiovascular conditions, prior cardiac interventions and surgeries

^c^Physical examination, includes height, weight and vital signs (blood pressure and heart rate)

^d^Includes re-interventions, potential valve-to-valve procedures, associated costs

^e^Solely performed at 1-year and 5-years of follow-up

^f^Solely documented at 5-years of follow-up

^g^Solely performed at baseline, 3–6 months and years 1 and 3 of follow-up

### Echocardiography core lab

Digital imaging and communication in medicine (DICOM) files of echocardiograms generated at years 1 and 5 will be collected for analysis by the Echo Core Laboratory to ensure unbiased and consistent analysis of the diagnostic data and, with the use of serial echocardiographic studies conducted on the same patient, for evaluating patient status over the course of 5 years.

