Primary endpoints	Time-related valve safety at 1 year (VARC-2)	Time to BVF due to SVD, defined as requiring re-intervention (redo surgery or ViV), or confirmed valve related death, according to Akin criteria [29]
	Rate of severe SVD (stage 3 following Salaun [24]) at 5 years (Echo CoreLab)	
Secondary endpoints	Haemodynamics and durability (Echo CoreLab) Clinical outcomes (NYHA and freedom from rehospitalisation) Quality-of-life (KCCQ & SF-12)	Early possible predictors of valve failure including leaflet calcification and morphological/haemodynamic valve degeneration: -Valve leaflet calcification via CoreLab evaluated MSCT (no contrast) -Haemodynamic performance (Echo CoreLab)

*BVF* Bioprosthetic valve failure, *EU* European Union, *KCCQ* Kansas City Cardiomyopathy Questionnaire, *MSCT* Multi-slice computed tomography, *NYHA* New York Heart Association, *SF-12* Short Form-12, *SVD* Structural valve degeneration, *US* United States, *VARC* Valve Academic Research Consortium, *ViV* Valve-in-valve

Up and beyond INDURE and RESILIENCE there is a third long-term data collection ongoing (IMPACT; NCT04053088) using the INSPIRIS RESILIA valve. It is being conducted in Germany, Austria, Switzerland and The Netherlands and will follow up to 500 patients for 5 years. The principal objective of IMPACT is the assessment of the impact of comorbidities such as chronic kidney disease (CKD), diabetes, hypertension, metabolic syndrome and inflammation on all-cause mortality. Among the secondary objectives there is, again, assessment of SVD, which will complement the data derived from INDURE and RESILIENCE.

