### Appreciation of the study design

The INDURE registry is a prospective, open-label, multicentre, international registry. The multinational nature of this registry increases the applicability of findings to clinical practice all over Europe and Canada. However, it has no control group making a comparison of different bioprosthetic valves or valve generations impossible. Furthermore, there is no comparison of the bioprosthetic valve data with the outcomes of mechanical valve implantation, which would be desirable, but goes beyond the possibilities of such a project. Because of the multicentre design, an Echo CoreLab has been established to have a uniform assessment of SVD over the time course of the 5-year follow-up. We considered establishing an MSCT CoreLab, as has been incorporated in the RESILIENCE trial, but it would have violated the non-interventional nature of the INDURE registry as most sites reported that an MSCT is not standard-of-care at their institution, which may be considered as a limitation. Nonetheless these data can be documented in case they are available from routine practice. Finally, the same INSPIRIS RESILIA valve will be used in all patients in the INDURE registry which will abolish any bias introduced by the use of different bioprosthetic valves.

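### The core lab reads only year-1 and year-5 echoes, so valves lost to structural degeneration in between have no core-lab reading for the 5-year primary endpoint; freedom is biased upward if those patients are dropped or censored

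*Protocol article*

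**What the plan says.** The Objectives section and Table 1 give the second primary objective as freedom from stage 3 SVD at 5 years, using the staging reproduced in Table 3. Table 4 (INDURE in perspective) lists the same endpoint as a rate of severe SVD "at 5 years (Echo CoreLab").

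On what the core lab receives, the Echocardiography core lab section states: "DICOM) files of echocardiograms generated at years 1 and 5 will be collected for analysis by the Echo Core Laboratory". Footnote e to Table 2, attached to the core-lab row, reads: "Solely performed at 1-year and 5-years of follow-up". The Appreciation of the study design section gives the purpose: "an Echo CoreLab has been established to have a uniform assessment of SVD over the time course of the 5-year follow-up".

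Other data are collected between those visits. Table 2 schedules a site transthoracic echo at baseline, at discharge and in the Years 1–5 column, with no footnote limiting the years. Serious adverse events are reported from surgery onward. The rehospitalisation row, from 3–6 months through year 5, carries the footnote "Includes re-interventions, potential valve-to-valve procedures, associated costs". Valve-related mortality and valve-related re-intervention are exploratory safety outcomes. The Statistical analysis section plans Kaplan-Meier analyses for survival and safety outcomes and does not name stage 3 SVD.

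The article does not say whether a re-intervention for SVD, a death from SVD or a stage 3 finding on a site echo between years 1 and 5 counts as an event, is censored or is excluded.

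**The concern.** Freedom from an event at 5 years is cumulative: it asks whether the event has occurred at any time up to year 5. A core-lab rate at year 5 is a snapshot of valves that can still be imaged. The two agree only if every valve that fails is still in place, in a living patient, at the 5-year visit.

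Stage 3 is the stage at which that is least likely. Table 3 describes it as generally clinically expressive, and the Discussion names valve replacement, valve-in-valve or death as the consequences of degeneration. The missing year-5 readings would then be caused by the endpoint itself, in the direction that favours the valve, on the durability question for which the registry exists.

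Timing also matters. A later analysis rule can decide how an interim re-intervention is counted, but it cannot supply a core-lab reading of images that were never sent. An explanted valve cannot be imaged again.

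**Working it through.** **1. Which patients lack a reading.** Table 3 and its notes define stage 3 haemodynamically as a change since implantation: a mean gradient rise of at least 20 mmHg with a marked fall in orifice area and velocity index, and/or regurgitation worsened by at least two grades to severe. Applied to a stage 3 valve arising at year 2, 3 or 4:

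| Course before the 5-year visit | Year-5 core-lab reading of the original valve | Consequence |
|---|---|---|
| Valve still in place, patient alive and attending | Yes | Still countable as stage 3; onset time lost |
| Replaced or treated by valve-in-valve for SVD | No | Missed unless counted from other data |
| Death from SVD | No | Missed unless counted from other data |

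Death from another cause also leaves no year-5 reading, but it is a competing event, not a missed SVD event.

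**2. The plan's own precision figures.** The article gives no precision for the 5-year endpoint. For the 1-year endpoint with N = 400, the half-width is 1.96 × √(p(1 − p)/400):
- p = 80%: 3.92 points, as stated.
- p = 99%: 0.98 points, stated as ±1%.
- p = 91.5%: 2.73 points, where the article states 2.14. This mismatch belongs to the 1-year endpoint and is not used here.

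The 99% figure serves below only as a yardstick for sampling error at high freedom.

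**3. Size of the effect if lost valves are left out.** The documents give no 5-year rate of SVD, re-intervention, death or dropout. All counts except N = 400 are therefore assumptions:
- 40 patients have no year-5 echo for unrelated reasons and are left out of both calculations.
- e = 4 valves in place are read as stage 3 at year 5.
- k further valves are replaced or fatal because of SVD between the two readings.

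Year-5 readings only: 1 − e/(400 − 40 − k). Lost valves counted as events: 1 − (e + k)/(400 − 40).

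| k | Year-5 readings only | Counted as events | Difference (points) |
|---|---|---|---|
| 0 | 1 − 4/360 = 98.89% | 1 − 4/360 = 98.89% | 0 |
| 2 | 1 − 4/358 = 98.88% | 1 − 6/360 = 98.33% | 0.55 |
| 4 | 1 − 4/356 = 98.88% | 1 − 8/360 = 97.78% | 1.10 |
| 8 | 1 − 4/352 = 98.86% | 1 − 12/360 = 96.67% | 2.20 |

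With e = 2 the differences for k = 2, 4, 8 are 0.55, 1.10 and 2.21; with e = 8 they are 0.54, 1.09 and 2.17. The result depends almost entirely on k. The year-5-only figure hardly moves as k rises, so the reported result would give no sign of the loss.

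**4. Kaplan-Meier does not by itself remove the problem.** If the k patients are censored at re-intervention or death and stage 3 is detected only at the year-5 reading, the risk set at year 5 is again 360 − k and the estimate is the year-5-only figure above.

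**The case against.** The strongest reply is that nothing in the article says interim failures are ignored. The objective itself carries no restriction to core-lab readings; the tie is a parenthesis in a Discussion table that compares two studies. Yearly site echoes, serious adverse events, re-interventions and valve-in-valve procedures are all collected. Kaplan-Meier methods are planned for safety outcomes, and SVD is among the exploratory safety outcomes. How an interim re-intervention is counted is an analysis rule that a condensed article may leave to the full protocol or analysis plan. This stands: a reader might infer that 5-year freedom will be overstated, but the article supports only that it would be if these patients were dropped or censored as non-informative.

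A reader might also infer that any valve failing between the two readings escapes the endpoint. The stage 3 definition does not support that, for the reason shown in the first table.

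Nor is the claim of uniform assessment over the 5-year course plainly contradicted. It can mean one reader across sites, with two serial studies per patient. That makes the schedule sparse, not inconsistent.

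Finally, the counts are assumed. The Background reports two earlier studies of the same tissue without SVD, one for up to 4 years. Those patients had mean ages of 65 to 67 years, so this does not settle the rate under 60, but it gives no support for the upper end of the range.

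What the reply does not reach is the reading schedule. It is fixed here by the word solely, with no event-triggered reading. Filling the gap from site data would give a mixed site and core-lab endpoint, unlike the one in Table 4.

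**Conclusion.** The point holds in conditional form. The article gives one primary endpoint both as cumulative freedom and as a core-lab rate at year 5, and it fixes a core-lab schedule that cannot provide a year-5 reading of a valve replaced, treated by valve-in-valve or lost through SVD-related death in between. If such patients are dropped or censored as non-informative, freedom is biased upward by about 0.5 to 2 percentage points for 2 to 8 such valves. The stated half-width at 99% freedom is about 1 point, so at 4 or more such valves the bias would be at least as large as the sampling error. With none, there is no bias. The size rests on assumed counts; the gap in the reading schedule rests on the text. Severity: should-fix.

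**What to change.** In the Echocardiography core lab section and footnote e to Table 2, add that the core lab also reads:
- the last available echo before any aortic valve re-intervention or valve-related death;
- any interim site echo, scheduled or not, on which stage 3 SVD is suspected.

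State the second primary endpoint in the same words in the Objectives section, Table 1 and Table 4: first stage 3 SVD at any time up to the 5-year visit. Count adjudicated re-intervention for SVD or death from SVD as an event even without a year-5 echo, and treat other deaths as competing events.

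The cost is a small number of extra reads at the existing core lab and DICOM uploads of echoes already taken. Patients undergo no added procedure, so the non-interventional design is kept. The upload instruction should reach sites while follow-up is running, since retrieving old files later is uncertain.
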